### Participant timeline

Table 1 shows the assessments at each time point following the SPIRIT statement [21]. Figure 1 demonstrates the flow chart of the study.

**Table 1 Tab1:**
[figure not shown]
Study assessments at specific time points

**Fig. 1 Fig1:**
[figure not shown]
Flow-chart of the study

### Usual care group

The control group will receive usual care including the wide range of care practices provided in the outpatient clinic at West China Hospital which are unrestricted by study protocols, which is in contrast to standard care may not reflect real-world care [23]. Participants in this group will be required to record treatment received using a log sheet weekly over the course of the study period. The common practice consists of a visit to a physiatrist or physiotherapist at outpatient clinic, verbal information about knee osteoarthritis and treatment options, prescription of pain medication, may involve physical or occupational therapy (e.g., manual therapy, physical agents) and advice about home exercises. All participants in the control group will be contacted via telephone or WeChat messenger (Tencent Holdings Ltd., Shenzhen, China) by an assistant who will provide instructions for the participant on how to finish the follow-up questionnaires and access the planned care they were seeking for knee osteoarthritis.

### eHealth intervention group

Participants assigned to the intervention group will, in addition to usual care, receive an invitation QR code via WeChat messenger to access the eHealth patient education tool built within the WeChat mini programs platform. Participants register themselves using a username and password. The intervention includes instructions on how to efficiently use the tool, information detailing the knowledge of knee osteoarthritis and the recommendations of clinical guidelines including level of evidence supporting each recommendation [24], and advice on healthy lifestyle, in a scheduled video conference with a physiotherapist using Tencent Meeting app (Tencent Holdings Ltd., Shenzhen, China) on a smartphone, a tablet or computer. Participants will be provided with a welcome brochure with an overview of the intervention components, and instructions on how to register and use the eHealth patient education tool and Tencent Meeting app (Web browser, Android or iOS app) at home. The intervention will be delivered within 7 days after the randomization, during which the video consultation with a physiotherapist will last up to 90 min according to the patient’s preference. Automatically generated push notifications within WeChat messenger will be sent to motivate participants to review the information and use the tool twice a week after the consultation for at least 6 months. Additionally, participants have the possibility to get help from the coordinators or via the study hotline regarding any technical problems when using the tool.

An iterative method of collaboration-based persuasive design between healthcare providers and patients is employed to the development of the eHealth patient education tool [18]. In brief, a focus group (*n* = 6, involved 3 patients with knee osteoarthritis, 2 physiotherapists and 1 physiatrist) was initially conducted in two phases during the development process, in which healthcare providers met at Phase I to provide input on the eHealth prototype regarding design and content and patients were invited to Phase II to discuss with healthcare providers regarding literacy demands and usability. Then a pilot-testing of the developed tool will be done among healthcare providers and patients (with a total of 20 participants) in a similar way to the focus group, and the testing version could be found in Additional file 2. The tool includes the following features:**Education Center:** information on knee osteoarthritis and treatment options (details could be found in Additional file 2), based on the recommendations of clinical guidelines; exercise advice and videos; physical activity and well-being advice.**Personal Information:** the option to record demographic data and history of knee osteoarthritis.**Self-Management:** self-monitor symptoms during the study; log the planned care received for knee osteoarthritis and other comorbidities.**Schedule and Plan:** set reminders and develop a calendar for the scheduled consultation, and assessments.**Communication and Help Center:** contact with an assigned physiotherapist or healthcare professional; an overview of the educational tool.

Participants who cannot attend the consultation will be excluded after contact has been attempted three times. One day after the consultation with the physiotherapist, all participants will receive the follow-up questionnaires on their WeChat. A reminder will be sent if participants are found non-responding after 1 week. Intervention fidelity will be assessed to rate the degree of involvement of a patient within 24 h after the physiotherapist-delivered consultation. As a participant reads information or watches a video, analytics built into the server website will collect data on what type of information and how long the participant spent on that. The chief research coordinator, program developer, and research assistance conducting data collection have access to the website and are able to view the analytics for each participant.

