**Methods:**

This study is a prospective randomized controlled trial with a 1:1 allocation in two groups. We will recruit 216 patients diagnosed with knee osteoarthritis from the outpatient physiatry/physiotherapy clinic at West China Hospital, Sichuan University in Southwest China. Both groups will receive usual care and additionally, the intervention group will use eHealth patient education tool during the process. Measurements will be taken at baseline, post-intervention, 1 month, 3- and 6-months follow-up. Primary outcome will be patients’ knowledge about disease and treatment options, measured by the validated osteoarthritis patient knowledge questionnaire. Secondary outcomes include patients’ satisfaction with the consultation, the eHealth patient education tool, and their trust of the physiotherapist.

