#### Other measures

Participants’ demographic data, history of diseases and health behavior information will also be collected. Potential “inadequate health literacy level” in participants will be screened using 3 questions: “how confident are you filling out questionnaires by yourself?” (“Confident with Questionnaires”), “Do you need someone to help you read? If yes, how often?” (“Read Assistance”) and “Do you have obstacles learning about your medical condition due to your inability to read? If yes, how often?” (“Problem Reading”) [28, 29]. In the process evaluation, measures of recruitment rate, attendance and follow-up rate will be monitored and recorded. Reasons for exclusions, declining participation and the drop-out of participants will be noted through the trial.

Participants in the eHealth intervention group will receive additional questions on the usability of the tool, including 13 closed questions and 3 opened-ended questions [30] and details of the questionnaire could be found in Additional file 4. Web-based analytics generated by the educational tool will be used to assess the utilization of the tool, which include data on content with which they engage, length of time spent on different content, and satisfaction ratings or feedback.

The measure of opinion and perspectives for participating the trial will be assessed via a phone- recorded interview (semi-structured) in both the eHealth and usual care group with the interviewee’s permission, for which a guide with open questions will be used to provide structure. The phone call will be made by a researcher who have experiences in qualitative interviews and is independent of the conduction of this trial. Two researchers (independent of the conduction of this trial) will be instructed by the interviewer to independently read and code transcribed texts line-by-line, from which codes generated will be sorted into themes and discussed to gain an overall understanding of any issue on difficulties and barriers to complete the trial. Any discrepancy will be resolved by the interviewer (senior researcher). During the trial, adverse events, medications and any other care received will be recorded using a log sheet, a sample could be found in Additional file 3.

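### Prompting to complete the follow-up questionnaires differs between the arms, so completion and timing of the self-completed knowledge score could differ too

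*Protocol article*

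**What the plan says.** All references are to the Methods of the protocol article.

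- **Common to both arms.** Outcomes are collected at five time points through an online link (Outcome assessment). One day after the consultation, "all participants will receive the follow-up questionnaires on their WeChat". The protocol adds: "A reminder will be sent if participants are found non-responding after 1 week". Both sentences stand under the heading eHealth intervention group, but neither is worded for one arm only, and I read them as covering both.
- **Intervention arm only.** The tool is given on top of usual care. Its Schedule and Plan feature is to "set reminders and develop a calendar for the scheduled consultation, and assessments". Push messages "will be sent to motivate participants to review the information and use the tool twice a week after the consultation for at least 6 months". This arm also gets "additional questions on the usability of the tool, including 13 closed questions and 3 opened-ended questions" (Other measures).
- **Control arm only.** Under Usual care group, every control is to be contacted by telephone or WeChat by an assistant who gives instructions on completing the follow-up questionnaires and also deals with the care the participant was seeking. No such questionnaire contact is described for the intervention arm. The coordinators and hotline offered there are for technical problems with the tool.
- **Blinding and missing data.** Participants know their group (Blinding). Multiple imputation is used for an outcome only when more than 5% of it is missing (Statistical analysis).

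**The concern.** In a trial whose primary outcome exists only if the participant opens a link and answers, how people are prompted is part of the measurement. It should be the same in both arms, so that any difference in scores comes from the education and not from who answered or when. Here one aid to answering sits inside the intervention and a different one sits in the control procedures.

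Two things are at stake. If the arms differ in who responds, and responders know more or less than non-responders, the comparison of mean knowledge carries a selection effect. If one arm answers systematically later, the two scores are taken at different distances from the consultation, when recall may differ. Analysis cannot fully repair either. Imputation removes only what the recorded variables explain.

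**Working it through.** **1. The two arms side by side**

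| Step | Intervention arm | Control arm |
|---|---|---|
| Questionnaires sent by WeChat | yes | yes |
| Reminder after 1 week without response | yes | yes |
| Calendar and reminder function covering assessments | available in the tool | none described |
| Assistant contact on how to finish the questionnaires | none described | all participants |
| Push messages | yes, to review information and use the tool | none described |
| Usability questions | 13 + 3 = 16 | none (no tool to rate) |

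The first two rows are the same. The third and fourth differ, in opposite directions: each arm has one aid to answering that the other lacks. The number and timing of the assistant contacts are not stated, nor is whether the calendar entries are automatic or set by the user. The two aids cannot be shown to balance.

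The fifth row adds little, since the stated purpose of the pushes is tool use. The sixth row is unavoidable in itself, because only tool users can rate the tool. It matters only if the 16 items come before or together with the knowledge form. The text does not give their order or visits, and Table 1 and Additional file 4 are not available here.

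**2. Size**

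The plan has no figure to reproduce. Its only input is one dropout allowance of 20%, not split by arm (Sample size). What follows is illustration under my own assumptions.

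Let m_I and m_C be non-response in the intervention and control arms, and g the gap in mean score between responders and non-responders, in SD, taken as equal in both arms. The responder mean exceeds the full-arm mean by m × g, so

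bias of the responder difference = (m_I − m_C) × g.

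With 20% loss overall and g from 0.25 to 0.8 SD:

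- 20% and 20%: 0 × g = 0.
- 15% and 25%: −0.10 × g = −0.025 to −0.08 SD.
- 10% and 30%: −0.20 × g = −0.05 to −0.16 SD.
- With the arms exchanged, the same sizes with a plus sign.

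Against the 0.5 SD used for the sample size, the non-zero cases run from 0.025/0.5 = 5% to 0.16/0.5 = 32%, in either direction. A minus sign means bias against the intervention. If non-responders were the better informed, every sign would reverse.

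These are complete-case figures. At 20% loss the 5% threshold is passed and multiple imputation would be used, so they do not describe the planned analysis. They show only what kind of effect is possible.

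**3. Power is not the issue**

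Power = Φ(0.5/√(1/n_I + 1/n_C) − 1.96), with 108 randomised per arm:

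- completion 80%/80% (86.4 and 86.4): 90.8%
- completion 85%/75% (91.8 and 81.0): 90.7%
- completion 90%/70% (97.2 and 75.6): 90.3%

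Uneven loss of this kind hardly changes power. The question is one of bias and timing.

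**The case against.** The strongest reply is that the routes that matter are already common: the same online link, the same time points, questionnaires to everyone by WeChat and a non-response reminder not limited by arm. The calendar is one listed feature of the tool. The text does not say that it sends reminders by itself or that it leads to the outcome link. Nothing says that the questionnaires are answered inside the tool. Controls also get personal contact about these very questionnaires, so they are not left without help. No passage gives completion by arm, and multiple imputation is planned at the expected level of loss.

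Most of this stands, and it limits the point. It does not remove it, because the common steps do not make the arm-specific ones equal. The control contact is a second difference, not a demonstrated counterweight to the first.

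A reader might infer more: that the intervention arm is actively reminded of assessments for six months while controls get a single message, and that the extra 16 questions lower its response. The documents do not support this. The pushes serve tool use, the calendar is described only as a function, controls have the assistant contact, and the position of the usability items is not shown. Nor do the documents support a numerical bias or a direction for it.

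**Conclusion.** The point holds in a limited form. As written, prompting and help with the follow-up questionnaires are not the same in the two arms: a calendar and reminder function for assessments in one, an assistant's instruction contact in the other. Because the primary score is self-completed online by unblinded participants, completion and answering dates could differ by arm.

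The net direction and size are unknown. The illustrative values rest on assumed non-response splits and score gaps and should not be cited as an estimate. The conclusion rests on two readings: that the WeChat delivery and the one-week reminder apply to both arms, and that the assistant contact on questionnaires is for controls only, since none is described for the other arm. Nothing here invalidates the design. It is an avoidable difference in outcome collection that is easy to remove beforehand and hard to correct afterwards.

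**What to change.** 1. Take the study assessments out of the tool's calendar. The consultation entry and the educational content can stay.
2. Give both arms the same questionnaire instructions, by the same means and at the same time. The other purpose of the control contact need not change.
3. Send both arms the same dated reminders from the questionnaire system, for example on the due date and after one week without response.
4. Report completion and completion dates by arm at each time point.
5. If it is not already so, open the usability items as a separate form only after the knowledge form has been submitted.

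Cost: changes to tool and questionnaire settings, best made before enrolment; a few extra automated messages; and the instruction contact for the 108 intervention participants, which takes some staff time. Sample size and analysis are unaffected.

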### Randomization and allocation

Eligible participants will be randomized with a one-to-one intervention allocation to the intervention (*n* = 108) or usual care (*n* = 108) group at the time of consent. Allocation concealment will be blinded and performed in the order of recruitment using a computer-generated random allocation schedule operated at the Centre for Biostatistics, Design, Measurement and Evaluation (CBDME) of West China Hospital, Sichuan University by a senior statistician after consent has been obtained. Random permuted blocks of sizes 4 or 6 will be employed to ensure participants are allocated to each group equally. Participants, research coordinators, and the eHealth physiotherapist will be notified, via a sealed opaque envelope, on which group the participant has been randomly assigned.

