### Statistical analysis

Summary statistics will be calculated and reported in accordance with the Consolidated Standards of Reporting Trial (CONSORT). The baseline comparability between groups will be tested among descriptive characteristics, as well as baseline outcome measures. The intention to treat analysis will be performed by a blinded statistician. Missing values will not be imputed unless the amount of that for an outcome is over 5%, for which multiple imputation will be performed. Quantitative data will be expressed as the Mean (SD), and number plus percentage will be used to describe nominal data. The treatment effect will be evaluated by the change in primary outcome between group analyses, using independent t-test and ANCOVA for quantitative variables and the χ^2^ test or the Fisher exact test to adjust for demographic data such as age, sex, education background, literacy level, joint symptoms, comorbidities, type and duration of treatment on change in outcomes. Repeated measure effect will be evaluated by the repeated measures ANOVA or generalized estimating equation, where applicable. Correlations between data on usability of the educational tool and patient reported outcomes will be analyzed using linear regression analysis within the intervention group. Constructivist grounded theory and a relational ethics lens will guide the plan for qualitative analysis [31]. The QSR NVivo 12 software will be used to organize and store the qualitative data. Memo-writing will be used to develop and refine key conceptual categories, outline themes under which each category lies and analyze relationships across these key conceptual categories. This conceptual framework will draw attention to understanding user experiences and engagement with the intervention in a context of relational settings. A statistical analysis plan will be posted on a public data repository before analysis.

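### Intervention participants who miss the post-randomisation video consultation are to be excluded, which conflicts with the stated intention-to-treat analysis

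*Protocol article*

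**What the plan says.** All references are to the protocol article.

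- **Randomization and allocation:** participants are assigned to the intervention or usual care "group at the time of consent", 108 to each.
- **eHealth intervention group:** "The intervention will be delivered within 7 days after the randomization". The education is given "in a scheduled video conference with a physiotherapist using Tencent Meeting app".
- **Same section, further down:** "Participants who cannot attend the consultation will be excluded after contact has been attempted three times".
- **Usual care group:** "All participants in the control group will be contacted via telephone or WeChat messenger". This contact is to explain the questionnaires and access to care. No attendance condition and no exclusion rule is attached to it.
- **Statistical analysis:** "The intention to treat analysis will be performed by a blinded statistician". Values are imputed (multiple imputation) only when more than 5% are missing for an outcome.

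**The concern.** An intention-to-treat analysis keeps everyone in the group to which they were randomised, whether or not they took up the treatment. A rule that excludes people for missing the main session of the intervention does the opposite, and here it is written for one arm only. The control arm keeps its counterparts, that is, the people who would have missed the consultation had they been allocated to it. The intervention arm loses them.

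If the people who miss a video call differ in disease knowledge from those who attend, the two arms are no longer comparable on the primary outcome. There is also a practical risk. Staff who read the sentence literally would stop sending questionnaires, and outcomes that were never collected cannot be recovered at the analysis stage.

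**Working it through.** **Order of events.** Consent and randomisation come first, the video consultation follows within 7 days, and exclusion follows three failed contact attempts. The exclusion is therefore after randomisation and depends on uptake of the allocated treatment.

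**Meaning of the word.** Participants and setting uses exclusion for people who never enter the trial. Other measures lists exclusions separately from drop-out. No section limits the rule to ending the intervention, and none says that follow-up or analysis continues.

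**Inputs for an illustration.** From the protocol: 108 per group, a planned difference of 0.5 SD and a two-sided 5% level. These are taken as given; no figure in the protocol is contested here. Assumed, because the documents do not give them: the share *f* of intervention participants who miss the consultation (5-20%), and the amount *g* by which non-attenders score below attenders (0-0.8 SD). Outcome data are taken as complete and the comparison as unadjusted.

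**Bias when the tool has no effect.** Set the mean of the full randomised population to 0 and the mean of attenders to *a*. Then (1 − f)·a + f·(a − g) = 0, so a = f·g. The controls average 0 and the remaining intervention participants average f·g, so the bias is f·g.

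| f | g = 0 | g = 0.5 | g = 0.8 |
|---|---|---|---|
| 5% | 0 | 0.025 SD | 0.04 SD |
| 10% | 0 | 0.05 SD | 0.08 SD |
| 20% | 0 | 0.10 SD | 0.16 SD |

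**False-positive rate at g = 0.5.** With unit SD in both arms, SE = √[1/(108(1 − f)) + 1/108], and the rate is P(Z > 1.96 − bias/SE) + P(Z < −1.96 − bias/SE).

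- f = 5%: SE = √(1/102.6 + 1/108) = 0.138; bias/SE = 0.18; rate 5.4%.
- f = 10%: SE = √(1/97.2 + 1/108) = 0.140; bias/SE = 0.36; rate 6.5%.
- f = 20%: SE = √(1/86.4 + 1/108) = 0.144; bias/SE = 0.69; rate 10.7%.

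**If the tool works.** Suppose that attenders gain 0.5 SD and non-attenders gain nothing. The intention-to-treat effect is 0.5(1 − f), which at f = 20% is 0.40 SD. The analysis without non-attenders estimates 0.5 + f·g, which at f = 20% is 0.50 SD (g = 0) to 0.66 SD (g = 0.8). Even with no gap, then, the two analyses answer different questions.

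**The case against.** The strongest reply is that the sentence does not say what people are excluded from. It could mean only that they receive no further intervention, while they stay in the randomised set and missing outcomes are imputed. The protocol also allows for 20% dropout. A reader might go further and conclude that the analysis would in fact be per-protocol under an intention-to-treat label. The text does not establish that; it shows two statements that conflict until one is clarified. But the benign reading is not written anywhere, and imputation helps only those who remain in the analysis set.

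The bias itself is not shown. It is zero if non-attenders know as much as attenders, and people may be unable to attend for reasons of scheduling. The planned ANCOVA covariates include age, education and literacy level, so adjustment could absorb part of any bias. A reader might also infer that the protocol itself predicts that non-attenders will be less literate or less engaged. It does not. The Discussion names only some participants over 60, with technological skill and attitudes to eHealth as examples of barriers. These objections stand against certainty about direction and size, but not against the conflict.

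Finally, a reader might infer that the post-intervention measurement (T1) is anchored differently in the two arms, because the video consultation exists in only one. The documents do not support that firmly. Usual care commonly includes a visit to a physiatrist or physiotherapist, satisfaction with the consultation is asked in both groups, and the text says: "One day after the consultation with the physiotherapist, all participants will receive the follow-up questionnaires on their WeChat". The clinic visit may serve as the anchor for controls. No change to a fixed calendar day for T1 is proposed; it would alter what T1 measures.

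**Conclusion.** The point holds as a conflict within the protocol. One arm has a post-randomisation exclusion for non-attendance, the other arm has none, nothing provides for follow-up or analysis of those excluded, and the stated analysis is intention-to-treat. This needs only the text and is firm.

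The consequence is conditional. If non-attenders have lower knowledge, the exclusion could favour the tool by up to 0.16 SD over the assumed range, about a third of the planned 0.5 SD (0.16/0.5 = 32%). The lower end of the range is zero. The false-positive rates above rest on assumed inputs, complete data and no covariate adjustment. They show what could happen and are not estimates for this trial.

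**What to change.** Replace the exclusion sentence with wording to this effect: *Participants who do not attend the consultation after three contact attempts are recorded as non-adherent. They stay in the trial, are sent the knowledge questionnaire at every time point, including T1, and are analysed in their randomised group. Any analysis without them is labelled per-protocol.*

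Non-attenders had no consultation, so the text should state when their T1 questionnaire is sent. Only the knowledge questionnaire needs to be required of them, since items on satisfaction with a consultation that they did not have would not apply.

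The cost in effort is small: 5-20% of 108 is about 5 to 22 people who receive further online links. The planned 108 per group does not change. The cost in effect size is real. If 20% do not attend and gain nothing, the estimated effect is 0.40 SD instead of 0.50 SD. With 108 per group, complete data and the normal approximation, power falls from 95.7% (0.50/√(2/108) − 1.96 = 1.71) to 83.6% (0.40/√(2/108) − 1.96 = 0.98).
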